### Participants

Strict inclusion criteria will be used to introduce homogeneity of the groups; therefore, participants enrolled in the study meet the following inclusion criteria:The participants rehabilitate from a proximal femur fracture following low energy trauma (e.g. fall from standing position).The participants have a prescribed unrestricted weight-bearing after (surgical) treatment of their fracture.The participants have an expected clinical rehabilitation duration of ≥ 2 weeks.The participants are aged ≥ 60 years.The participants have a bodyweight ≤ 120 kg.

Participants with the following criteria will be excluded from the study:People with cognitive impairment, defined as a score < 18 on the Mini Mental State Examination (MMSE) [16].People who are readmitted to the hospital within two weeks after study participation, for example for infectious complications.People with co-morbidities that affected gait significantly before the proximal femur fracture.

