This trial is a two-arm, parallel-design, prospective RCT. Based on a previous pilot study, the average length of rehabilitation is 44 days, with a standard deviation of 17. Using a power of 0.80, an alpha of 5%, and an expected reduction of seven days (one week) in two-sided testing, a sample size of 94 participants per group was calculated. Participants will be allocated to either the control group or the intervention group using a stratified cluster randomization according to the sealed opaque envelope principle. First, all rehabilitation clinics were divided into two groups depending on the inclusion rate: < 2 vs. ≥ 2 eligible participants per month. This division was made to avoid skewing of inclusion rate in both arms. Then in both groups, clinics were randomized by the principal investigator into the control or intervention group using the sealed opaque envelope principle. This resulted in six rehabilitation clinics in the control group and five rehabilitation clinics in the intervention group (Table 1). Randomization per center, or cluster randomization, was chosen for two reasons. First, individual selection bias by the physical therapist is minimized. Second, and more importantly, the physical therapists and participants within one center can now provide a single treatment, either care as usual or care as usual, with real-time visual biofeedback. Considering the constant interaction between physical therapists, as well as between participants, individual randomization would increase the risk of data collection errors.

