### Protocol

Data will be gathered according to a strict study protocol (Fig. 1). Candidate patients who fulfill the inclusion criteria will be asked to participate in the study by the site investigator and receive an information letter with the study protocol and study objectives. If patients agree to participate in the study, informed consent will be signed and the cognitive score will be evaluated by the MMSE. The MMSE is an objective score to quantitatively asses the severity of cognitive impairment. A MMSE score < 18 indicates severe cognitive impairment [16] and this leads to exclusion of the patient in this trial. After informed consent and MMSE, data will be collected from participants according to the following trial protocol. The institutional protocol for physical therapy after proximal femur fractures will be followed in all participants. In addition, each participant receives daily force measurements using the SensiStep system in a 30-m walk to measure the gait parameters. Additional clinical tests will be executed to gain additional insight in the rehabilitation progress of each participant:Functional Ambulation Categories (FAC, once per week)Elderly Mobility Scale (EMS, twice per week)Visual Analogue Scale (VAS, daily)

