### Statistical analysis

Statistical analysis on outcome measures will be conducted using Statistical Package for the Social Sciences (SPSS). First, data distribution will be assessed. Second, missing data will be handled by a multiple imputation technique. The primary analysis will be based on an intention-to-treat principle. Also, a per-protocol analysis will be performed as sensitivity analysis to assess the robustness of the results to protocol deviations [17]. The primary goal is to find a relation between the gait parameters (maximum peak load and step duration) and the discharge date. In addition, other spatiotemporal gait parameters measured by the SensiStep will be analyzed for this relation as well. The secondary goal is to find a relation between the gait parameters and the clinical measurements (i.e. EMS, FAC, and VAS). Relations between all data will be examined using multiple regression analysis.

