### Monitoring

This trial will be conducted according to the principles of the Declaration of Helsinki (amended version by the 64th WMA General Assembly, Fortaleza, Brazil, October 2013) and in accordance with the Medical Research Involving Human Subjects Act. Gathered data will be encrypted and stored on a secure server and is accessible by the Steering Committee.

This trial will be conducted under strict supervision of an experienced Steering Committee from the University Medical Center Utrecht (UMCU), Maastricht University Medical Center+ (MUMC+), and Uppsala University (UU). Acting as a Steering Committee, the principal investigators from UMCU and MUMC+ will discuss the progress of enrollment at least once every two weeks. The Steering Committee will perform a blinded interim analysis on 30%, 60%, and 90% of the included participants. During these interim analysis, reasons for exclusion will be discussed with the site investigators. Other items will be discussed as well, including but not limited to, applied discharge criteria for each patient, adverse events, quality of the retrieved data, missing data, and necessity to include other participating centers.

A monthly newsletter will be written by the Steering Committee and distributed among the participating centers. In this newsletter, the inclusion rate will be shown per center, which is a common and effective way to increase awareness and readiness to include patients in multicenter trials. The trial progress and general results will be communicated by the Steering Committee upon request.

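### Early hospital readmission is listed as an exclusion from the study, but it can only happen after allocation, so the rule conflicts with the intention-to-treat primary analysis

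*Protocol article*

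**What the plan says.** The Participants section introduces its exclusion list with "Participants with the following criteria will be excluded from the study". One of the three items is "People who are readmitted to the hospital within two weeks after study participation, for example for infectious complications". The other two are a low cognitive score and co-morbidity that already impaired gait before the fracture.

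On timing, the Study design section says that "clinics were randomized by the principal investigator into the control or intervention group using the sealed opaque envelope principle", so a patient's arm follows from the clinic. The Protocol section says "After informed consent and MMSE, data will be collected from participants according to the following trial protocol", and measurement is then daily. In intervention clinics, feedback is given during those same walks (Interventions).

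On analysis, the Statistical analysis section says "The primary analysis will be based on an intention-to-treat principle". It adds that "a per-protocol analysis will be performed as sensitivity analysis to assess the robustness of the results to protocol deviations" and that "missing data will be handled by a multiple imputation technique".

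The Monitoring section says "During these interim analysis, reasons for exclusion will be discussed with the site investigators" and names adverse events among the other items for discussion. No section says that patients readmitted early stay in the intention-to-treat set.

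**The concern.** An exclusion criterion should be decidable before, or independently of, the treatment being compared. This one depends on what happens in the first two weeks on study. Applied as written, it selects patients on a post-allocation event, and the groups analysed may no longer be the groups allocated.

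Two features make a difference between arms possible. Participants and therapists know the arm (Outcome measures). In intervention clinics, feedback and therapist also encourage loading towards full bodyweight from the start, so an effect on early complications cannot be ruled out, although the documents show none.

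The event bears on what the trial measures. The primary gait outcomes are analysed in relation to discharge date, and the sample size rests on a 7-day reduction in length of rehabilitation. Patients who go back to hospital early are likely to have an atypical length of stay and gait course, so removing them can move the comparison.

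**Working it through.** **The plan's own figure.** Inputs from Study design: SD 17 days, difference 7 days, two-sided alpha 5%, power 0.80.

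n per group = 2 × (1.960 + 0.842)² × 17² / 7² = 92.6, so 93 by the normal approximation. The t-test solution is 93.55, so 94. The stated 94 per group is reproduced, and the sample-size arithmetic is not at issue here.

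**Order of events.**

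| Step | Section | Before or after allocation |
|---|---|---|
| Clinic assigned to an arm | Study design | allocation itself |
| Consent and cognitive test | Protocol | after; the test is not a consequence of study treatment |
| Daily walks, with feedback in intervention clinics | Protocol; Interventions | after |
| Readmission within two weeks | Participants | after, during treatment |

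The phrase about two weeks after participation is loose, but any reading places the event after allocation. The window is not a short run-in either: 14 / 44 = 32% of the mean length of rehabilitation.

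**Possible effect on length of stay.** Let p_I and p_C be the proportions readmitted early, and D the difference in recorded stay between readmitted and other patients, taken as equal in both arms. Then

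all-patient difference (intervention − control) = difference among patients not readmitted + (p_I − p_C) × D.

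Exclusion leaves only the first term, so it removes (p_I − p_C) × D. The documents give neither p nor D. Every value of p and D below is an assumption.

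| Assumed p_I v p_C | Assumed D (days) | Term removed (days) | Share of 7 days |
|---|---|---|---|
| equal | any | 0 | 0% |
| 12% v 6% | +14 | 0.06 × 14 = 0.84 | 12% |
| 12% v 6% | +20 | 0.06 × 20 = 1.2 | 17% |
| 10% v 5% | +14 | 0.05 × 14 = 0.7 | 10% |
| 15% v 5% | +21 | 0.10 × 21 = 2.1 | 30% |
| 12% v 6% | −30 | 0.06 × (−30) = −1.8 | 26%, opposite sign |

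The last row covers a transfer that ends the recorded stay: about 14 days instead of 44, so D = 14 − 44 = −30. The article lists length of stay in the rehabilitation clinic among the items documented, but does not say how a hospital episode is counted.

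Where D is positive, exclusion favours the arm with more early readmissions; where D is negative, it works against that arm.

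**The case against.** The best defence is that analysis sets are usually defined in a statistical analysis plan, which is not shown. Exclusion from the study might then mean only that measurement stops, with data kept or imputed. That reading is possible, but the article states both rules. Its plain wording removes these patients from the study, and nothing in it reconciles that with intention to treat. This is a rule stated wrongly rather than a detail left out.

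Several stronger conclusions are tempting, and the documents do not support them:

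- **That exclusion favours biofeedback, or always favours the arm with more complications.** This needs readmitted patients to have longer recorded stays. The documents do not say so, and the sign reverses if a transfer closes the stay.
- **That unblinded staff decide who is readmitted.** The article says only that participants and therapists cannot be blinded. It does not say who decides on readmission.
- **That biofeedback causes early harm.** The article's own example is infection, and all participants in both arms have unrestricted weight-bearing.
- **That safety events are lost.** Exclusions and adverse events are discussed at the interim looks. This answers much of the safety worry, but it does not put the patients back into the primary analysis.
- **That power falls to 76%.** Removing 10% leaves 94 × 0.90 = 84.6 per group, with power 0.764 (normal) or 0.759 (t), before any allowance for clustering. The 10% is assumed, and so is the absence of replacement. The abstract's 94 measured per group can be read as 94 evaluable.

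**Conclusion.** The concern holds as an inconsistency in the primary analysis set. The eligibility section removes patients for an event after allocation, while the analysis section promises intention to treat. Followed as written, the plan conditions on something that treatment could affect.

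The size and direction of any bias are unknown. Under the assumed values, the shift in the length-of-stay difference runs from zero (equal rates and equal added stay) through 0.8 to 1.2 days (12% v 6%, 14 to 20 extra days) to 2.1 days in the most extreme case tried. It is about 1.8 days the other way if a transfer ends the recorded stay. These are illustrations, not estimates, and the documents contain no evidence that the arms differ in readmission. The case for change rests on the conflict between the two rules and does not depend on any of these figures.

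**What to change.** 1. Remove hospital readmission from the eligibility exclusions.
2. State that all consented patients who meet the baseline criteria are in the intention-to-treat set, readmitted or not. Use the multiple imputation already planned for their missing gait data.
3. State in advance one rule, the same in both arms, for counting length of stay across a hospital episode. Without it, the sign of the effect on the comparison is undetermined.
4. Report the number of early readmissions, with reasons, by arm.
5. Apply the two-week exclusion only in the per-protocol sensitivity analysis already planned.
6. Where consent allows, recover the discharge dates of patients already removed.

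**Cost.** A short amendment to the eligibility and analysis text, some data retrieval (limited by what consent permits), and a somewhat more variable outcome. The amount of added variability cannot be calculated from the documents. The change concerns who is analysed, not how patients are treated.

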### Protocol

Data will be gathered according to a strict study protocol (Fig. 1). Candidate patients who fulfill the inclusion criteria will be asked to participate in the study by the site investigator and receive an information letter with the study protocol and study objectives. If patients agree to participate in the study, informed consent will be signed and the cognitive score will be evaluated by the MMSE. The MMSE is an objective score to quantitatively asses the severity of cognitive impairment. A MMSE score < 18 indicates severe cognitive impairment [16] and this leads to exclusion of the patient in this trial. After informed consent and MMSE, data will be collected from participants according to the following trial protocol. The institutional protocol for physical therapy after proximal femur fractures will be followed in all participants. In addition, each participant receives daily force measurements using the SensiStep system in a 30-m walk to measure the gait parameters. Additional clinical tests will be executed to gain additional insight in the rehabilitation progress of each participant:Functional Ambulation Categories (FAC, once per week)Elderly Mobility Scale (EMS, twice per week)Visual Analogue Scale (VAS, daily)

**Fig. 1 Fig1:**
[figure not shown]
Schedule of enrolment, interventions, assessments, and documentation. MMSE Mini Mental State Examination, EMS Elderly Mobility Scale, FAC Functional Ambulation Categories, VAS Visual Analogue Scale

Finally, additional information of each participant will be documented, including the following:Date of surgeryType of surgeryCo-morbiditiesWalking aidLength of admission to the rehabilitation centerAgeGenderLengthWeight

### Interventions

Participants in the intervention group receive, in addition to the standard institutional protocol, real-time visual feedback about weight-bearing during the 30-m walk with SensiStep. The physical therapist has real-time visual insight in the weight-bearing as well by observing the tablet together with the participant. Both the biofeedback system (visually) and the physical therapist (verbally) assist and motivate the participant to adapt the weight-bearing to the optimal level. The target weight will be set at 100% bodyweight, as the participants have no restrictions in weight-bearing.

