**Methods:**

This is a two-arm, parallel-design, prospective, randomized controlled trial. Inclusion criteria are age ≥ 60 years, a proximal femur fracture following low energy trauma, and unrestricted-weight bearing. Exclusion criteria are cognitive impairment and limited mobility before trauma. Participants are randomized into either the control group, which receives care as usual, or the intervention group, which receives real-time visual biofeedback about weight-bearing during gait in addition to care as usual. Spatiotemporal gait parameters will be measured in 94 participants per group during a 30-m walk with an ambulatory biofeedback system (SensiStep). The progress of rehabilitation will be evaluated by the primary outcome parameters maximum peak load and step duration in relation to the discharge date. Secondary outcome parameters include other spatiotemporal gait parameters in relation to discharge date. Furthermore, the gait parameters will be related to three validated clinical tests: Elderly Mobility Scale; Functional Ambulation Categories; and Visual Analogue Scale. The primary hypothesis is that participants in the intervention group will show improved and faster rehabilitation compared to the control group.

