Therefore, in this randomized controlled trial (RCT), real-time visual biofeedback will be provided to the patient and healthcare professional in the clinical setting by the ambulatory biofeedback system SensiStep (Evalan BV, Amsterdam, The Netherlands). This biofeedback system was previously validated in static and dynamic situations [15]. In short, the system consists of an in-sole force sensor, which is able to measure weight-bearing reliably and continuously during gait. Generated peak loads are directly translated into a LED signal, to provide real-time feedback to the patient. The same signal is sent to a tablet, resulting in a real-time graphical illustration of each step shown to the healthcare professional. By using this biofeedback system, patients can be guided to the optimal level of weight-bearing. This potentially leads to better functional outcome, as well as improved fracture healing through mechanotransduction.

In this RCT, it will be investigated whether elderly patients recover faster or better after proximal femur fractures if they receive real-time visual biofeedback in the clinical setting. The control group receives care as usual and the intervention group receives care as usual with the addition of real-time visual biofeedback to improve weight-bearing to the optimal level. Hypothetically, patients in the intervention group show: (1) an increase in maximum peak loads; and (2) faster step durations at an earlier timepoint in their rehabilitation. Furthermore, patients in the intervention group recover faster, which results in an earlier discharge date.

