### Outcome measures

The primary outcome measures are the gait parameters maximum peak load (in %bodyweight) and step duration (in seconds), which will be analyzed in relation to the discharge date from the rehabilitation center. It is expected that the intervention group will show an improvement in gait parameters and earlier discharge date compared to the control group. The discharge date will be determined by a multidisciplinary team within the usual institutional regime, irrespective of the study protocol. Secondary outcomes include other spatiotemporal gait parameters and validated clinical tests, including the EMS, the FAC, and the VAS. The EMS is a standardized validated scale for assessment of frail elderly people. The FAC is used as a diagnostic and evaluative tool to assess the physical performance of patients. The VAS is a commonly used, subjective scale to assess the amount of pain patients experience. Spatiotemporal gait parameters measured by the SensiStep will be correlated to the clinical test scores (e.g. EMS, FAC, and VAS). Blinding the participants and/or physical therapist is not possible, as both users are aware of the biofeedback they receive in the intervention group. However, data will be encrypted and anonymously delivered by the Steering Committee to the data scientists, which makes the data scientists blinded for the analysis of gathered data.

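### The primary gait outcomes are measured in the same walk in which the intervention arm gets live feedback, so an arm difference cannot separate on-device performance from lasting recovery

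*Protocol article*

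**What the plan says.** **Measurement.** Under Protocol, "each participant receives daily force measurements using the SensiStep system in a 30-m walk to measure the gait parameters". The Abstract (Methods) likewise places the gait measurement in a 30-m walk with SensiStep, for 94 participants per group.

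**Treatment.** Under Interventions, the intervention group receives "real-time visual feedback about weight-bearing during the 30-m walk with SensiStep". The same section says: "Both the biofeedback system (visually) and the physical therapist (verbally) assist and motivate the participant to adapt the weight-bearing to the optimal level". It also fixes the goal: "The target weight will be set at 100% bodyweight". The Background describes the contrast between arms: "The control group receives care as usual and the intervention group receives care as usual with the addition of real-time visual biofeedback". It adds that the peak loads picked up by the in-sole sensor drive the LED shown to the patient.

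**Outcome and reading.** Outcome measures names two primary gait parameters: maximum peak load, as a percentage of bodyweight, and step duration, in seconds. Both are to be analysed in relation to the discharge date. The Abstract uses them to judge how rehabilitation progresses, and its primary hypothesis is that the intervention arm recovers better and sooner.

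**Blinding.** Outcome measures states that participants and therapists cannot be blinded and that the data scientists will be.

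**The concern.** Only one kind of 30-m walk is described, and it serves as both treatment session and measurement session. In the intervention arm the patient is shown a loading target, and urged towards it, while the loading is being recorded. One of the two primary outcomes is that same quantity on that same scale. The control arm is not described as having this.

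A patient who loads the leg more only while watching the display would look, in these data, like a patient who has recovered more. If such a response exists, a positive gait result could be reported as improved rehabilitation when nothing carries over once the device is off. No feedback-off first walk is described either, so change from the first session does not remove the problem.

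**Working it through.** **1. Is it the same walk?** Protocol: daily SensiStep measurement in a 30-m walk, all participants. Interventions: feedback during the 30-m walk with SensiStep, intervention group. The use of the definite article and the absence of any second walk in the text make these the same occasion.

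**2. Is the fed-back quantity the outcome?** For maximum peak load, yes: the LED reflects peak load, the target is 100% bodyweight, and the outcome is peak load in % bodyweight. For step duration, no: it is not displayed. It could change indirectly if patients alter their gait to reach the load target, but the document gives neither a size nor a direction for that.

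**3. What does the arm difference contain?** Write the expected difference in a gait parameter on a feedback-on walk as

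difference = L + M,

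where L is the lasting gain from training and M the immediate effect of display and prompting. Feedback-on walks identify only the sum. A walk with feedback off in both arms would identify L. Blinded data scientists do not help, because M enters when the walk is recorded. More participants estimate L + M more precisely but do not split it.

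**4. The plan's own figure.** Study design gives SD 17 days, a reduction of 7 days, two-sided 5% and power 0.80.

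- Normal approximation: n = 2 × (1.960 + 0.842)² × 17² / 7² = 92.6, so 93 per group.
- The t-test version gives 93.55, so 94, as stated. Power at 94 is 0.806.

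This calculation concerns length of rehabilitation, not gait. The document gives no SD or expected effect for peak load or step duration.

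**5. Illustration of M (assumptions, not estimates).** Set L = 0 and let M be a shift of d SD in a simple two-arm comparison of means, 94 per arm, two-sided 5%, clustering ignored. The standard error is √(2/94) = 0.146 SD, and the chance of significance is Φ(d/0.146 − 1.960) plus a negligible opposite tail, except at the smallest d.

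| Momentary shift d (SD) | Chance of a significant gait difference |
|---|---|
| 0 | 5% |
| 0.1 | 10.5% |
| 0.2 | 27.8% |
| 0.3 | 53.9% |
| 0.4 | 78.3% |
| 0.5 | 92.9% |

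About 80% is reached at roughly 0.41 SD. That is simply the difference detectable at 94 per arm (7/17 = 0.41) and says nothing about how large M is.

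**6. Effect of clustering on the illustration.** Eleven clinics were randomised, so 188/11 = 17.1 patients per clinic. With assumed ICCs of 0.02 and 0.10 and equal clinic sizes, the design effects 1 + 16.1 × ICC are 1.32 and 2.61. A cluster-adjusted analysis would then find a shift of 0.41 SD significant with about 69% and 42% probability. The separation problem in step 3 is the same at any ICC.

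**The case against.** Several objections are sound and limit the point.

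- **Performance with feedback on is partly what the trial studies.** The Abstract speaks of therapy compliance and of the effect of biofeedback on gait. For those aims, loading during feedback sessions is a legitimate outcome. This stands. The difficulty arises only when the same data are read as recovery, as the primary hypothesis does.
- **A reader might infer that no feedback-off measurement exists at all.** The documents do not support that. Fig. 1 is the schedule of assessments and is not shown, and the article condenses a fuller protocol. The supportable statement is that the text describes none.
- **A reader might infer that the whole case for faster rehabilitation is contaminated.** It is not. Outcome measures leaves the discharge date to a multidisciplinary team working independently of the study protocol, and EMS, FAC and VAS are listed as separate tests. They are unblinded, but this mechanism does not directly affect them.
- **A reader might infer that both primary outcomes are equally affected.** Only peak load is fed back. For step duration the effect is possible but indirect.
- **A reader might infer that the momentary effect passes unchanged into the primary analysis.** That holds for a direct comparison of gait between arms. Statistical analysis states a multiple regression relating gait to discharge date and does not give the form of the arm comparison, so the exact route is not fixed. The intervention arm's gait values would still carry the on-device component into that regression.
- **Coaching of controls.** All participants follow institutional physiotherapy, and the article does not say that controls get no encouragement or that their display is off. The contrast is inferred from feedback being defined as the added element and from the prompting being described for one arm only.

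**Conclusion.** The point holds for the gait outcomes as described. With feedback and prompting inside the measured walk in one arm, an arm difference in maximum peak load, and possibly in step duration, cannot separate the immediate effect of the device from lasting recovery. By itself it supports only the narrower aim about weight-bearing or compliance while feedback is on.

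The size of any on-device effect is unknown from the document. The figure of about 0.41 SD for about 80% probability is illustrative: it assumes no lasting effect, a simple comparison of means and no clustering. The conclusion rests on the text alone and would change if the schedule in Fig. 1 or the full protocol contains a feedback-off walk.

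**What to change.** **Remaining participants.** Take the gait outcome for the arm comparison from 30-m walks already scheduled: the first session and one fixed day a week, for example the weekly FAC day. On these walks hide the LED and tablet and use the same neutral instruction in both arms. Use the first such walk as baseline covariate. Keep feedback-on walks as process data on loading during training.

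**Participants with feedback-on data only.** Report the gait contrast as performance with the device on. Rest any claim of faster recovery on outcomes recorded outside the feedback walk. This matters in practice: recruitment began in March 2017 and was to end around August 2018, and the article appeared in April 2018, so an amendment would come too late for many.

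**If Fig. 1 or the full protocol already has a feedback-off walk,** say so in the text and name it as the source of the primary gait outcomes.

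**Cost.** A short procedural amendment with no extra walk or equipment. About one feedback session a week is forgone in the intervention arm, each patient contributes fewer outcome points, and the therapists conducting the walks remain unblinded.
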